| **DURATION OF THE SEARCH** | Length of Inclusion Period: 2021 – 2023  Duration of participation of each participant: 12 weeks Total duration of the research: 3 years |
| **ANALYSIS**  **STATISTICS OF**  **DATA** | Descriptive, mean, standard deviation and extent or median and interquartile analysis will be presented for quantitative variables. For qualitative variables, it will be a question of number and percentage.  For comparative analyses between the 2 groups:   - The non-parametric Wilcoxon Mann-Whitney test will be performed for quantitative variables - The nonparametric Wilcoxon test for paired data will be used for before-and-after comparisons for quantitative variables - The Chi2 test (or Fisher if theoretical < 5) will be performed for the qualitative variables - The McNemar test will be used for before-and-after comparisons for qualitative variables. |
| **EXPECTED BENEFITS** | To date, it is clear that very few good quality studies have been carried out on the subject. Here we propose to scientifically and rigorously evaluate foot reflexology in order to reach reliable conclusions in pain in Parkinson's patients. The challenge is to provide concrete help to Parkinson's pain patients and to enable doctors to recommend this type of care in an informed manner. |

*in ON condition; that is to say, at least one hour after taking the anti-parkinsonian treatment for the treatment to be fully effective.

AbstractThis research has been registered in http://www.clinicaltrials.gov/.

Exploratory study of the impact of foot reflexology on chronic pain in parkinsonian patients. University Hospital Toulouse is the sponsor of this research.

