## SECONDARY OBJECTIVES

The secondary objectives are:

1. To compare the number of patients with at least 30% improvement in pain on VAS after management between the 2 groups of patients (FR vs SM).
2. To compare the kinetic variation in the analgesic effect of a 4-session PR treatment on the intensity of chronic pain measured by a Visual Analogue Scale (VAS) during management between the 2 groups of patients (FR vs SM).
3. Comparing the variation in chronic pain using King's Parkinson's disease Pain

Scale (KPPS) and the Brief Pain Inventory (BPI), and the Primary Parkinsonian Pain Diagnostic Questionnaire (3PDQ) before and after the overall management between the 2 groups of patients (PR vs. MS).

1. Compare the evolution of the subjective nociceptive threshold and the tolerance to heat using the thermotest between the 2 groups of patients (FR vs SM):

a) before and after overall support between V1 and V4

1. Compare analgesic consumption using a diary of analgesic treatments throughout the study, before and after treatment between the 2 groups of patients (FR vs SM).
2. To compare pain acceptance with CPAQ-8, anxiety and depression with HAD, before and after management between the 2 groups of patients (PR vs. MS).
3. To determine if there are biomarkers of the effect of RP on brain activity using fMRI before and after management between the 2 groups of patients (RP vs MS).
4. To assess whether there are personality traits that modulate the analgesic response in the 2 groups of patients (according to the results obtained in the TCI personality test)

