From the Intensity-Response curve, we will be able to determine the temperature for which the VAS was equal to 75%. This temperature will then be applied twice at five-minute intervals to the patient, who will have to orally express his tolerance threshold (which corresponds to the time before the stimulation becomes unbearable).

1. Consumption of analgesics by means of a collection booklet throughout the study (collection of the prescribed treatment and dosage).
2. At the deltas of the following scores, before and after global management:
   - CPAQ-8 pain acceptance test *[McCracken 2004]*. This self-questionnaire assesses the acceptance of chronic pain via 8 statements. Each item is rated between 0 (never true) and 6 (always true).
   - of the HAD scale *[Lépine 1985]*. It is a self-questionnaire to screen for anxiety/depressive disorders. Patients answer 14 questions: 7 about anxiety and 7 about depression. It is an assessment that measures mild to moderate depression in PPs *[Schrag 2007].*
3. Comparison between the structural and activation maps of brain networks in order to identify biomarkers of the management of brain activity. The modulation of brain activity will also be assessed by means of a map of correlation coefficients representing the strength of connectivity between the different brain networks and regions of interest, obtained from functional MRI sequences at rest, [after – before] care. The main MRI sequences performed will be resting state acquisitions (resting functional imaging) and anatomical imaging (i.e. T1 imaging).
4.
[figure not shown]
Comparison between the 2 groups of patients of their analgesic response according to their personality profile.

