The 15 patients in each group will benefit from an fMRI before the first session of FR vs SM at the Baudot technical platform.

**Following all these evaluations, the patient will benefit from the 1st session of PR, or MS, performed by the reflexologist.**

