**THIS CALCULATION WAS CARRIED OUT BY THE RESEARCH METHODOLOGICAL SUPPORT UNIT.**

### STATISTICAL METHODS USED

Data analysis:

The data processing that will be carried out will be in accordance with the MR-001 reference methodology and therefore meets the CNIL and GDPR expectations, the data in this study will be pseudonymized and protected. A randomization list will be created to randomly determine patient groups.

A detailed flow-chart will describe the flow of subjects in the study. In particular, the number of subjects screened for eligibility, the number of eligible subjects, the number of subjects included and followed up at each visit will be mentioned. The reasons for refusal to participate and to leave the study will be described at each stage.

A descriptive analysis of the entire recruited population will be carried out to verify if there are any deviations from the protocol at the time of inclusion. Quantitative variables will be expressed as ± average standard deviation, range, medians and interquartile ranges, and qualitative variables will be expressed as numbers and percentages.

The analysis is conducted on the intention-to-treat population.

To meet the main objective, we will first describe the VAS score at Baseline (V1) and after all PR sessions (V5) by means of a "box plot" graph. This is in order to better understand the distribution of scores in the 2-stroke and in the 2 groups (as well as 4 box plots). Then we will calculate and describe the variations between V5 and V1. The variation between V1 and V5 is defined by the crude delta between these 2 visits. Finally, we will perform a non-parametric Wilcoxon Mann Whitney test to compare the distribution of variations between the 2 groups of patients.

To meet the secondary outcomes:

1. We will calculate the number of patients with a minimum of 30% improvement on the VAS score between V1 and V5. Thus, if (V5-V1)/V1 is greater than or equal to 30%, the patient is considered to be a responder. We will compare these responder rates between the 2 groups of patients using a Chi2 test.
2. We will perform a non-parametric Wilcoxon Mann Whitney test to compare the distribution of variations at each visit (delta with baseline) between the 2 groups of patients: i.e. 4 tests.
3. For the KPPS and BPI scores and the 3PDQ, we will perform the same analyses as the primary outcome because they are quantitative scores.

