4. For the subjective pain perception threshold to heat and heat tolerance. We will perform the same analyses as the primary outcome as these are quantitative scores. 5. For the consumption of analgesics, which will be considered as several qualitative variables (e.g. taking paracetamol yes/no, aspirin taking yes/no), we will compare the proportion of patients taking each analgesic between the 2 groups by means of Chi2 tests.
5. The analyses regarding the CPAQ-8 score will be the same as those for the primary objective as it is a quantitative score. As the anxiety and depression scores of the HAD scale are quantitative variables, they will be analysed in the same way as the primary outcome.
6. As imaging results are quantitative variables, we will analyze them in the same way as for the primary purpose.
7. Personality profile results will be analyzed using a nonparametric Wilcoxon Mann Whitney test

For the study as a whole, the significance threshold is set at 0.05 (bilateral).

The statistical analysis will be conducted by [name] from the MeDatAS – CIC – CHU Toulouse team. Analyses will be conducted using SAS analysis software version 9.4 or later.

All analyses of neuroimaging data will be carried out within the ToNIC unit (Inserm/UPS UMR1214):

- the structural and activation images obtained in MRI for each subject will be normalized and smoothed using the Statistical Parametric Mapping ((SPM) software Wellcome Department of Cognitive Neurology, University College, London, UK).
- The resting state images fMRI will be analyzed using a model-dependent method called "seed-tovoxels" using the Conn software version 18b (https://www.nitrc.org/projects/conn). The seeds will be determined according to anatomical atlases to identify the brain areas of interest (default mode network, sensorimotor network). The connectivity between these seeds and the rest of the brain voxels will be explored.

These images will then be used to perform a t-corrected test for multiple comparisons to compare the cards [after – before] support. Thus, the intensity and size of the synchronous activity of brain areas functionally connected to the areas of interest of the reflex zones stimulated on the foot can be determined. Areas of interest are defined anatomical areas in known and classic stereotactic spaces in neuroimaging.

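### The fMRI objective compares reflexology with sham, but the only image-level test names no arm and differs from the protocol's other imaging instruction; one between-arm test should be stated

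*Protocol*

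**What the plan says.** - **Objective (Protocol, section 3, Secondary objectives; also in the Research summary).** The imaging aim is "To determine if there are biomarkers of the effect of RP on brain activity using fMRI before and after management between the 2 groups" (RP is the French abbreviation for foot reflexology). This is a comparison between arms.
- **Outcome (section 4, Secondary outcomes).** The connectivity measure is a map of correlation coefficients "obtained from functional MRI sequences at rest, [after – before] care". That sentence names no arm, although the stem above the list of secondary outcomes refers to both arms.
- **First analysis instruction (section 11, Statistical methods used, list of secondary analyses).** "As imaging results are quantitative variables, we will analyze them in the same way as for the primary purpose". The primary method in the same section reads: "we will perform a non-parametric Wilcoxon Mann Whitney test to compare the distribution of variations between the 2 groups of patients". It carries no multiplicity correction.
- **Second analysis instruction (section 11, closing paragraph on neuroimaging).** After the seed-to-voxel processing, the images are used to "perform a t-corrected test for multiple comparisons to compare the cards [after – before] support". In this translated text, 'cards' evidently means maps and 'support' means the course of care. Neither an arm nor a group-by-time contrast is mentioned.
- **Summary of methods (section 1).** Paired tests are also foreseen: "The nonparametric Wilcoxon test for paired data will be used for before-and-after comparisons for quantitative variables".
- **Numbers (section 9, inclusion visit).** "The 15 patients in each group will benefit from an fMRI before the first session of FR vs SM". The monitoring table places the two scans at V1 and V5.

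**The concern.** The sham arm is there to remove what both arms share: touch, attention, the therapist, time and repeat scanning. Section 2 (Justification of methodological choices) gives placebo and therapist-interaction effects as the reason for it. A test of after against before, whether in the FR arm or in all patients pooled, leaves that shared part in. Correcting for multiple comparisons does not help, because it controls error over voxels for whatever contrast is tested and does not change the contrast.

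Two features make the ambiguity matter in practice. Section 11 assigns all neuroimaging analysis to the imaging unit, and the paragraph written for that unit is the one that leaves out the arms. The sentence after the t-test then interprets the result in terms of the reflex zones stimulated on the foot, whereas section 7 describes the sham massage as not stimulating those points. A reflexology-specific interpretation is thus attached to a test that does not mention sham. Section 2 (Expected benefits) intends these data to suggest imaging biomarkers and to support a larger project, so a non-specific signal could be carried forward.

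**Working it through.** **Step 1: the two instructions side by side.** The protocol gives no numerical figure for the imaging analysis, so there is nothing to reproduce.

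| | Imaging item in the list | Neuroimaging paragraph |
|---|---|---|
| Test | Mann-Whitney (rank) | t-test |
| Contrast as worded | FR vs SM on V5-V1 change | after vs before; no arm named |
| Multiplicity correction | none in the primary method | yes |
| Data level | not stated | whole-brain maps |

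No sentence ranks the two or assigns each to its own kind of imaging data.

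**Step 2: what a before-after reading would do, for one measure.**

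Inputs:
- Two-sided level 0.05 (section 11).
- 15 patients per arm scanned (section 9), and 12 per arm as the number that the size calculation requires (section 11).
- *Assumption, not in the documents:* the true change is the same in both arms, so there is no FR-specific effect.
- *Assumption, not in the documents:* within-arm power p for that shared change is 50% or 80%.

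The arms are independent, so P(FR significant, SM not) = p(1-p):
- p = 0.50: 0.50 × 0.50 = 0.25
- p = 0.80: 0.80 × 0.20 = 0.16

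**Step 3: simulation over a range of shared change.** The sizes, in SD of the individual change, are assumed because the documents give none. Changes are normal; 20,000 runs, 4,000 for Mann-Whitney. Each cell is the share of trials significant at 15 / 12 per arm, with no true FR-SM difference.

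| Shared change | FR arm alone, before-after | Both arms pooled, before-after | FR significant, SM not | FR vs SM t-test | FR vs SM Mann-Whitney |
|---|---|---|---|---|---|
| 0 | 5% / 5% | 5% / 5% | 5% / 5% | 5% / 5% | 5% / 5% |
| 0.3 SD | 19% / 16% | 35% / 29% | 15% / 14% | 5% / 5% | 4% / 4% |
| 0.5 SD | 44% / 35% | 75% / 65% | 25% / 23% | 5% / 5% | 4% / 5% |
| 0.8 SD | 82% / 72% | 99% / 97% | 15% / 21% | 5% / 5% | 4% / 5% |
| 1.0 SD | 95% / 88% | 100% / 100% | 5% / 10% | 5% / 5% | 4% / 4% |

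The formula agrees with the simulation: at 0.5 SD and 15 per arm, p = 0.444 gives 0.444 × 0.556 = 0.247, against 25% simulated.

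The between-arm test holds its level whatever the shared change; the before-after tests do not. All figures are per single measure, before any voxelwise correction.

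**The case against.** The strongest reply is that the protocol already fixes FR vs SM for imaging in three places: the objective, the stem of the secondary-outcome list, and the item that sends imaging to the primary method. Section 4 uses the bracketed after-minus-before expression as subtraction notation, so the disputed sentence can mean that difference maps are compared, and the comparison named elsewhere is between arms. The two instructions could also be complementary: a rank test for summary values and a corrected t-test for maps. Much of the second-level model is properly detail for an analysis plan.

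Most of this stands. A reader might infer that the plan excludes an FR vs SM image test, or that the two instructions cannot coexist; neither follows. A reader might also infer that an uncorrected voxelwise Mann-Whitney test is planned, or that a significant FR map will be set against a non-significant SM map. The protocol proposes neither, and its only voxel-level paragraph specifies a correction.

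What the reply does not remove is that the sentence defining the image test omits the arms, and that the division of labour between the two instructions is nowhere stated. This is not a gap left to a later plan, since the protocol itself states both methods.

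**Conclusion.** The point holds as an inconsistency in section 11. The objective is between arms, the image-level test does not say so, and a second instruction prescribes a different test without saying which one decides. Followed literally, the image test would not separate an FR effect from change shared with sham.

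Its size can only be illustrated: a 25% chance of 'FR significant, SM not' at an assumed within-arm power of 50%, and 16% at 80%, for one measure with equal true change in the arms. It would be tempting to use 2p(1-p), which gives 50% and 32%, but that also counts trials in which only SM is significant, and those could not be presented as an FR biomarker. Neither power comes from the documents, and neither figure carries over directly to a corrected whole-brain analysis.

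Severity is minor to moderate. One exploratory secondary outcome of a pilot study is affected; the primary VAS analysis is not.

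**What to change.** In section 11:

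1. Reword the neuroimaging paragraph so that the image-level test is FR vs SM on each patient's V5-V1 seed-to-voxel difference map (the group-by-time contrast), keeping the correction for multiple comparisons.
2. Limit the instruction to analyse imaging like the primary outcome to prespecified region-level summary values.
3. Label within-arm after-minus-before maps as descriptive.

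The cost is wording only; scans and software stay the same. The real downside is power. With 15 per arm, the standard error of a within-arm mean change is SD/√15 = 0.26 SD, while that of the FR-SM difference is SD × √(2/15) = 0.37 SD, and the difference contains only the FR-specific part of the change. That loss is inherent in asking the question that the objective poses.

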#### 12. OVERSIGHT OF RESEARCH

RP is a very well-tolerated non-drug intervention. There will be no oversight committee for this study.

**13. RIGHTS OF ACCESS TO SOURCE DATA AND DOCUMENTS**

### ACCESS TO DATA

Acceptance of participation in the protocol implies that the investigators will make available the documents and individual data strictly necessary for the monitoring, quality control and audit of the research, available to persons with access to these documents in accordance with the legislative and regulatory provisions in force.

### SOURCE DATA

All information contained in original documents, or in authenticated copies of such documents, relating to clinical examinations, observations or other activities carried out in the context of research and necessary for the reconstruction and evaluation of the research. The documents in which the source data is saved are called the source documents. All rating scales will be entered directly into the CRF.

### DATA PRIVACY

In accordance with the legislative provisions in force, persons with direct access to the source data will take all necessary precautions to ensure the confidentiality of information relating to investigational medicinal products, research, persons who are eligible for it, and in particular with regard to their identity and the results obtained. These people, like the investigators themselves, are subject to professional secrecy.

During the research or at the end of the research, the data collected on suitable persons and transmitted to the sponsor by the investigators (or any other specialized stakeholders) will be anonymized. They must not under any circumstances display the names of the persons concerned or their addresses in plain text.

The methods of coding the participants will be: the first letter of the subject's first and last name will be recorded, accompanied by a coded number specific to the research indicating the number of the group and the order of inclusion of the subjects by group.

The sponsor will ensure that each person who participates in the research has given his or her written consent for access to the individual data concerning him or her that is strictly necessary for the quality control of the research.

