## JUSTIFICATION OF METHODOLOGICAL CHOICES

Critics of non-drug interventions and FR claim that the effect is only placebo or related to management and patient/therapist interaction. This is why, in the present study, we propose to study the impact of FR management compared to a sham massage (SM), with the same reflexologist practitioner, in order to avoid a bias related to the personality of the therapist and therefore to the patient's care.

In addition, the patient will be informed that he or she will be randomly selected to benefit from an analgesic NPI, explaining that two different techniques are being studied in this protocol. The patient will thus be blinded.

In order to ensure objective evaluation and blinded data analysis, the person in charge of pain assessment of Parkinson's patients will not be informed of the patient's randomization. This is why we talk about double-blind in this study.

The rigorous evaluation of pain in this study led us to select many questionnaires that evaluate the different aspects of pain. This will allow us to cross-reference the different information in order to strengthen the observation of the impact of the management of FR.

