**5. RESEARCH DESIGN**

## RESEARCH OUTLINE

Due to the lack of published data on the subject, it was chosen to conduct a pilot study, since FR has not yet been evaluated in a population of Parkinson's patients in order to reduce their chronic pain.

It is therefore a single-center, longitudinal, prospective, double-blind, randomized exploratory study in 2 parallel groups (1:1 ratio): 1 group benefiting from FR sessions, 1 control group benefiting from foot MS sessions. Both the patient and the pain assessor will be blinded.

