## METHODS FOR RANDOMIZATION

Patients will be randomized into two groups in a 1:1 ratio, the experimental group that will receive the FR sessions and the control group that will receive the foot SM.

Randomization will be established by the MeDatas cell of the Clinical Investigation Center (CIC). When a subject is included, the assignment of a number and group will be established by means of a secure randomization interface via the CIC website.

Subjects will be randomized once the investigator verifies that they meet the eligibility criteria (Section 5). Patients will be randomized to one of 2 groups according to the chronological order of inclusion of patients in the protocol.

Randomization will be done at the inclusion visit. Only the person in charge of foot reflexology and sham massages ([name]) will be informed of the patient's randomization.

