### DATA MANAGEMENT

The information will be collected for each subject on a paper report book filled in by the investigators and members of the research team. This notebook includes the identification of the subject (pseudonymized code) and the follow-up data. A source document (file created for the purposes of the study) will be kept for each subject participating in the study; The observation and medical follow-up concerning the study will be recorded in this document. This source document will be retained by the principal investigator.

All brain imaging data from the study are stored on computer media by the investigating physicians or their delegates and analyzed under the responsibility of [name] (ToNIC).

The observation notebook of each patient will be kept under the control of the principal investigator in the neurology department of the University Hospital, and will be reviewed by the ARC monitoring on site, before being sent to the member of the team responsible for the entry (ToNIC). Data entry will be supervised by the study's scientific leader. The terms and conditions of entry will be defined jointly with the Project Manager. Data entry and data analysis will be carried out by the MeDatAS – CIC – CHU Toulouse unit for the statistical part and by ToNIC for the MRI part.

The data will be validated in accordance with the data management plan defined jointly by the principal investigator, the data manager and the statistician of the study.

The data freeze will be performed once all data has been collected and entered and all queries have been resolved.

The unblinding can then be carried out.

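### The participant code carries the group number onto the case report form, which conflicts with assessor blinding and with unblinding only after data freeze

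*Protocol*

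**What the plan says.** **The code.** Protocol section 13, Data privacy, defines it as the participant's initials together with a study code number "indicating the number of the group and the order of inclusion of the subjects by group".

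**Where the code goes.** Section 14, Data management, says of the paper case report form: "This notebook includes the identification of the subject (pseudonymized code) and the follow-up data". Section 13, Source data, adds: "All rating scales will be entered directly into the CRF". The same section 14 has investigators and research-team members fill in the form, which then passes to the monitor and on to data entry and analysis.

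**The groups.** Section 5, Methods for randomization: "Patients will be randomized into two groups in a 1:1 ratio".

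**The blind.**
- Section 5, Research outline: "Both the patient and the pain assessor will be blinded".
- Section 9, End-of-research visit, has a clinical research associate assess pain blinded. This is the V5 visit, which supplies the second half of the primary outcome.
- Section 5, Methods for randomization, limits knowledge of the allocation to the practitioner who gives the sessions.
- Section 2, Justification of methodological choices, explains why the assessor is kept uninformed: "In order to ensure objective evaluation and blinded data analysis".
- Section 14, Data management, after describing the freeze: "The unblinding can then be carried out".

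**A related statement.** Section 9, Inclusion visit / randomization process, has the randomisation website return to the investigator both the participant number and the procedure group allocated.

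**The concern.** A participant identifier in a blinded trial should carry no information about treatment. Here the coding rule builds the group into the identifier, and the identifier travels with the form on which outcomes are recorded. Anyone who handles two or more forms can see which patients belong together.

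The practitioner necessarily knows the arm, so the double-blind description rests on the patient and the assessor. The primary outcome is a subjective pain rating on a VAS, which the annex has staff obtain by asking the patient. An assessor who knows or suspects the arm could influence how the question is put or the answer encouraged. The same code would be in view while queries are resolved before the freeze, when decisions about the data should be made without knowledge of group.

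**Working it through.** No formula applies. The check is whether the statements can all be true together.

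1. **Does 'group' mean treatment arm?** The trial is single-centre with two parallel groups. The protocol uses the word for the reflexology and sham arms and defines no other grouping of participants. So the group number in the code is the arm, up to its label.

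2. **Does the code reach the assessor?** Data privacy defines the participant code, Data management puts the pseudonymized code on the form, and Source data has the rating scales entered there directly. Whoever records the ratings therefore works on a form bearing the code. Nothing says that the group element is masked, scrambled or left off the assessor's copy.

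3. **When is the code assigned?** Section 9 places the inclusion evaluation after randomisation. A group-bearing code can therefore be on the form for both the V1 and the V5 ratings, the two halves of the primary outcome.

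4. **What does the code reveal?** By itself it splits the 30 planned patients into two sets of 15, without saying which set is which. One identified patient supplies the label:
   - with a group-free number, one slip reveals 1 patient of 30;
   - with the group number, the same slip reveals that patient and the 30 − 1 = 29 others, including those not yet enrolled.

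5. **Is such a slip plausible?** The protocol itself offers three routes.
   - Section 7 lists calf work in the sham procedure only; the reflexology steps concern the foot and malleoli. A patient who mentions the calves to an assessor who knows this difference gives the label away.
   - Section 9 allows sham patients a reflexology session after they finish. Staff who learn of one such session learn which number is sham.
   - The website gives the investigator the number together with the procedure group, and investigators help fill in the form.

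6. **Side by side.** A code showing the group on the form cannot be squared with an assessor kept unaware of the allocation, with knowledge confined to the practitioner, or with a blind lifted only after the freeze. Separately, the website's message to the investigator contradicts the practitioner-only rule outright, whatever the code looks like.

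**The case against.** **The code shows a number, not a treatment.** This stands. A reader might infer that every form openly discloses reflexology or sham. The text does not support that: the arm label needs one further piece of information. What remains is that a single leak decodes the whole trial.

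**The operational number may be a different one.** The randomisation and inclusion-visit sections list the number and the group as separate outputs of the website, and the second calls the number unique. Data management says only that the code is pseudonymized. The form might therefore carry a group-free number. But the only description of what the participant code contains is the one in Data privacy, and nothing says that another is used. The uncertainty is itself a reason to correct the text.

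**The statistician and data-entry staff are never said to be blinded.** Also true. A reader might infer a breach of a stated blind for them. The protocol defines double-blind as patient and assessor; for the others, blinding is implied by the aim of blinded analysis, the practitioner-only rule and the post-freeze unblinding. The MeDatAS unit also both sets up the randomisation and runs the statistical analysis, so for that unit the code is not clearly the decisive leak.

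**Not every visit is covered.** The blinded research associate is named only in the V5 section; the section on V2 to V4 does not say who collects the VAS. The conflict is best documented for V5.

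**The bias cannot be sized.** It is tempting to convert an assumed shift in VAS into an inflated false-positive rate. The protocol gives no basis for the shift, and the VAS is the patient's own rating, so an assessor acts on it only indirectly. The standard deviation of 1.5 in section 11 is given for the VAS in Parkinson's patients, not for the V1 to V5 change. The planned test is Wilcoxon Mann-Whitney, so a t-test calculation would not describe it. Any such figure would be false precision.

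**Conclusion.** The point holds as an internal contradiction. As written, the coding rule puts a group identifier on the form in which outcomes are recorded, and this conflicts with the blinded assessor, practitioner-only knowledge of allocation and post-freeze unblinding. Its reach is all 30 planned patients, because one identified patient can reveal the rest. Its effect on the result cannot be quantified from the document.

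The conclusion rests on two readings: that the pseudonymized code on the form is the one defined under Data privacy, and that group there means treatment arm. Both are the natural readings, and nothing in the protocol contradicts them. It does not rest on any claim that the code spells out the treatment, that the statistician's blinding is explicitly promised, or that bias has occurred. The correction is cheap and protects a blind that the protocol states explicitly, so it should be made.

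**What to change.** 1. In section 13, Data privacy, replace the rule with one study-wide sequential number in order of inclusion, with no group element and no within-group order.
2. State that the key linking number to group is held only in the randomisation system and by the practitioner until after the data freeze.
3. Reconcile section 9, Inclusion visit / randomization process, with section 5, Methods for randomization: the website should return only the participant number to the investigator and send the allocated group to the practitioner alone. Without this, changing the code leaves the more direct leak open.

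**Cost.** Changes of wording in sections 9 and 13, and a small change to the numbering and notification settings of the randomisation site. No visit, assessment or patient procedure changes.
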